## Abstract

**Background:**

Meeting the ambitious UN 90–90-90 HIV testing, treatment and viral load suppression targets requires innovative strategies and approaches in Sub-Saharan Africa. To date no known interventions have been tested with community health workers (counsellors) as social franchisees or owner-managed businesses in Community-based HIV counselling and testing (CBCT) work. The aim of this methods paper is to describe a Social franchise (SF) CBCT implementation trial to increase HIV testing and linkage to care for individuals at community levels in comparison with an existing CBCT programme methods.

**Methods/design:**

This is a two arm non-randomised community implementation trial with a once off round of post-test follow-up per HIV positive participant to assess linkage to care in low income communities. The intervention arm is a social franchise CBCT in which unemployed, self-employed or employed community members are recruited, contracted and incentivised to test at least 100 people per month, identifying at least 5 HIV positive tests and linking to care at least 4 of them. Social franchisees receive approximately $3.20 per HIV test and $8 per client linked to care. In the control arm, full-time employed HIV counsellors conduct CBCT on a fixed monthly salary. Primary study outcomes are HIV testing uptake rate, HIV positivity, Linkage to care and treatment rate and average counsellors’ remuneration cost. Data collection will be conducted using both paper-based and electronic data applications by CBCT or SF counsellors. Data analysis will compare proportions of HIV testing, positivity, linkage to HIV care and treatment rates and counsellors’ cost in the two study arms.

**Discussion:**

The study will provide important insight into whether the SF-delivered CBCT programme increases testing coverage and linkage to care as well as reducing CBCT cost per HIV test and per HIV positive person linked to care.

**Trial registration:**

Pan African Clinical Trial Registry PACTR201809873079121. The trial was retrospectively registered on 11 September 2018.

## Background

South Africa has consistently remained the country with the largest number (7.9 million) of people living with HIV globally. More than 1 in five (20.6%) adults (15–49 year olds) live with HIV [1]. An incidence of 1.00 has been reported among the 15–24-year-old people of which women have disproportionately higher incidence (1.51) than men (0.49). This incidence translates to 200,000 adults infected with HIV annually as at 2017 [1]. The UNAIDS estimate that 86% of the people living with HIV in South Africa know their HIV status and only 56% are on treatment while less than half (45%) are virally supressed [2]. Only 29% of men aged 15–49 and 17% of women have never tested and 59% of women and 45% of men tested and received results in the last 12 months [3]. Although HIV testing rates have increased over the last decade, low levels of testing, treatment and viral suppression in an HIV epidemic country need urgent improvement to meet the UN’s 90–90-90 targets. The pandemic varies by place in South Africa with as high as 27% prevalence in KwaZulu-Natal province and as low as 12.6% in the Western Cape Province while Gauteng province, where our proposed trial will be conducted, has a 17.6% HIV prevalence. Gauteng province has the second lowest rates of HIV testing for women (54%) and third lowest for men (41%) in South Africa [3]. The province accounts for a third (34.2%) of all annual HIV deaths in the country and lower (75%) than national average (86%) proportion of people who know their HIV status [4]. Only 55% are on treatment and 46.4% are virally suppressed. Without new or strengthened HIV prevention interventions the province will not meet the three UN HIV targets for testing, treatment and viral suppression [4].

The Department of Health (DoH) through its national, provincial and district structures provides a framework for and direct the provision of HIV testing services (HTS) to all people in South Africa through health facilities (private and public). HTS are provided through health facilities and community-based services. In the latter, clients are reached in homes, workplaces and public community places such as educational institutions. Since the advent of antiretroviral therapy, HIV testing was initially solely conducted by clinicians and nurses in health facilities. Facility-based HIV testing however suffered from enormous individual, relationship, community and health system barriers leading to low levels of HIV testing uptake and treatment including missing people at high risk and delaying treatment [5–7]. To address this, community-based HIV counselling and testing (CBCT) approaches were introduced that saw an increase in HIV testing and ART uptake in South Africa [8–10]. See Table 1 for definitions of terms used in this paper. Also, to increase the number of people in the HIV testing and treatment, clinicians and nurses were replaced by lay counsellors. CBCT in South Africa relies on a cadre of workers, loosely termed counsellors, mostly employed by or volunteering with non-governmental organisations. These cadres, coined community health workers (CHWs), numbered 40,000 in South Africa in 2004, almost equal in number to the nurses in public health facilities (43,000) [11], and rose to 73,000 in 2011 [12, 13] In 2006, the WHO introduced a quick win strategy for HIV care work by task shifting HIV work to CHWs. To date, studies have shown the success of this cadre in CBCT including increased rates of HIV testing uptake, reaching people with high CD4 count, reaching first time testers and linking clients to care [14–20]. CHWs have been described as the backbone of workers in HIV testing [21, 22]. One of the challenges facing CBCT programmes include the absence and inadequate health information infrastructure to enhance clients’ (re) linkage to care and support [23]. Due to below optimum levels of testing and treatment, South Africa still requires more innovations to achieve universal test and treat goals enshrined in the 90–90-90 UN targets adopted by South Africa, despite implementing CBCT with lay councillors over the last decade.

**Table 1 Tab1:** Definitions of terms used in the study

Terms	Description
Community-based HIV counselling and testing (CBCT)	HIV testing services offered outside of the health facilities but in the community where people live or work. HIV testing services include a general package that includes mobilising clients for testing, consenting, testing, counselling and disseminating HIV prevention services and relevant referrals
Community health workers (CHWs)	Members of the community selected, employed or volunteering to provide basic preventive, promotional and rehabilitative health and medical care to their community members
Health facility-based HIV counselling and testing	HIV testing services offered at the health facilities including consenting, testing, counselling and disseminating HIV prevention services and relevant referrals. Health facilities refers to public and private health clinics. They offer services defined below under HIV testing services.
HIV testing services	These include pre-counselling, testing, post-counselling, condom distribution, sexual behaviour change and communication, referral for care and treatment including medical male circumcision, pre-exposure prophylaxis, HIV treatment. These will be customised per participant’s situation including test result.
Key population	Groups of people defined and known to be of greater risk of HIV infection than the average members of the community. These include MSM, FSWs, people who inject drugs (PWID), transgender people and People in Prisons or other enclosed settings.
Mobile Application	A mobile device such as a tablet loaded with application software that includes the use of GPS triangulation and a questionnaire to collect, save and transmit respondents’ data to enable real-time reporting and informed decision-making
Participant mobilisation	Marketing and informing clients about HIV testing services to create demand for HIV testing services. Mobilisation will be conducted by CBCT team members before and on the day of testing in each community where HIV testing is conducted. Mobilisation will include promotion and awareness campaigns using loud inhalers, distributing pamphlets, erecting banners and talking to passers-by about HIV testing services offered and inviting them to test for HIV.
Social Franchise (SF)	“a network of private individuals/ providers that are linked through agreements to provide socially beneficial health services under a common franchise brand”. A ‘franchisor’ manages the brand and oversees the administration of the program while a “franchisee” implements the brand according to laid down rules
Systematic Home-Based testing and counselling	Mapping Households at the community level and offering door-to-door HIV testing services to household members in the target community. The process was done systematically through visiting all houses, one after the other, in a community in order to avoid missing any dwelling.

Social franchising of health services has increasingly been adopted by the health sector from the commercial industry to address the universal access to health for all by 2015. The concept of social franchising aims to increase coverage, affordability and effectiveness of services by using a commercial relationship between the franchisor and franchisee [24, 25] The franchisor, who owns the brand, defines a product and brand, delivery mode, quality assurance, quality standards and provides a brand and staff training while a franchisee implements the product work under the franchisor’s guidance and brand name and product [26]. To date no known interventions have been tested with community health workers (counsellors) as social franchisees or owner-managed businesses in CBCT work. CBCT requires working with people who live and work in the community, people with knowledge of the community hotspots and requires empowering these cadres to prepare them for sustainable CBCT work once the NGO funding ends. To this effect, the Foundation for Professional Development (FPD) designed a brand called Social franchise community-based HIV counselling and testing (SF CBCT) in 2016 for piloting in comparison with the generic FPD CBCT programme [27] to increase HIV testing and treatment opportunities for individuals at community level. In this paper, we present the methodology for a SF CBCT trial within an existing FPD CBCT programme. The methodology allows for testing for differences in the use of the mobile electronic data application system to capture client data for linkage to HIV care and treatment purposes as implemented by both FPD and SF counsellors additionally.

## Methods

### Design

The study is a two arm non-randomised community implementation trial with a once off round of post-test follow-up per HIV positive participant to assess linkage to care. Clients will be tested by one of the HIV testing strategies – either by an existing FPD counsellor or a SF HIV counsellor under the sub-contracted model. Each study arm has 19 counsellors conducting CBCT. The overall study design is illustrated on Table 2.

**Table 2 Tab2:** Process flow for the FPD and Social Franchise HTS

Item	Activity	FPD	Social franchise
1. Counsellor Recruitment and contracting	Contract	1. Employed by FPD 2. Normal employment contract 3. Normal payroll contract 4. Work for 8 h a day	1. Unemployed, self-employed or employed elsewhere, not employed by FPD 2. Contracted by franchisee-franchisor contract 3. No restriction on hours, days worked 4. Test >/= 100 people per month 5. Test>/5 HIV + tests per month 6. Link >/= 4 HIV + clients per month
	Remuneration	1. Fixed monthly salary	1. Paid $3.20 per HIV test 2. Paid $8 per HIV + client linked
	Training	Training focussed on: 1. Pre-test, test, post-test, documentation, referral and linkage to care	Training focussed on: 1. Pre-test, test, post-test, documentation, referral and linkage to care 2. business development & management
2. Mobilisation	Community level mobilisation	Community events; flyers; campaigns (e.g. couples counselling); conducting systematic door-to-door mobilization campaigns distributing flyers, and condoms	Community events; flyers; campaigns (e.g. couples counselling); conducting systematic door-to-door mobilization campaigns distributing flyers, and condoms
	Individual level mobilisation	Informing households on the benefits and availability of testing for HIV; scheduling household level testing appointments and/or actively recruiting clients for same day HTS	Informing households on the benefits and availability of testing for HIV; scheduling household level testing appointments and/or actively recruiting clients for same day HTS
3. Documentation	Questionnaire and database	Questionnaire interview on: 1. Personal Data 2. Demographic characteristics 3. HIV testing history 4. HIV test results 5. HIV prevention and risk 6. TB/STI screening 7. Referral 8. Linkage to care 9. (bi) monthly, quarterly, annual reports	Questionnaire interview on: 1. Demographic characteristics 2. HIV testing history 3. HIV test results 4. TB/STI screening 5. HIV prevention and risk 6. TB/STI screening 7. Referral 8. Linkage to care 9. (bi) monthly, quarterly, annual reports
	Payment	Paid per normal payroll	Monthly payment claims to franchisor
4. Basic package of services	Pre-test	1. Information and education 2. Screening 3. Condom education and distribution	1. Information and education 2. Screening 3. Condom education and distribution
	Test	1. Informed written consent 2. HIV testing using national algorithm	1. Informed written consent 2. HIV testing using national algorithm
	Post-test	1. tailor-made counselling based on test result(s) and life situation 2. referral for psychosocial support 3. referral for HIV treatment and care 4. development of tailored linkage plans and timelines looking at individual barriers and concerns 5. if negative: risk reduction counselling, appropriate HIV prevention services	1. tailor-made counselling based on test result(s) and life situation 2. referral for psychosocial support 3. referral for HIV treatment and care 4. development of tailored linkage plans and timelines looking at individual barriers and concerns 5. if negative: risk reduction counselling, appropriate HIV prevention services
5. Follow up	Referral to HIV care and treatment	Discuss referral health facility	Discuss referral health facility
	Linkage and service update	Actively follow up to verify and document linkage to care	Actively follow up to verify and document linkage to care

### Setting

The study will be conducted in the designated project areas with high population densities (between 3200 and 7400 people square kilometre compared to district average of 1110 people per square kilometres) (http://worldpopulationreview.com/world-cities/pretoria-population/), low income, rural, urban and peri-urban settlements in Tshwane metropolitan city, South Africa’s administrative capital. Tshwane district is resident to 3.3 million people with young people (15–34 years) making up 37% of the total population (Mid-Year Population Estimates 2016, Stats SA). An estimated 24.3% live in poverty (http://www.statssa.gov.za). Tshwane’s HIV epidemic requires attention and it is characterised by (i) a low HIV testing coverage of 21.6% which is below national average (23%), (ii) a 2.4% increase in the proportion of people living with HIV from 2016 to 2017; (iii) a third highest attrition rate (out of all districts of South Africa) of people on antiretroviral therapy that is well below the national average of 58.9% and low male condom distribution [28]. The study will be conducted in three of the seven sub districts in the Tshwane metropolitan city. These sub-districts were purposively selected because of their higher than average HIV prevalence and population densities. A significant population lives in dense housing, with poor access to electricity and water. These sub districts have a predominantly black African population. In terms of health, Tshwane district is among the 27 priority districts, referred to as high HIV burden districts, with high HIV incidence and prevalence within South Africa’s 52 districts.

### Participant inclusion criteria

In each study arm any person aged 12 months or older, living in the study community and not having tested for HIV in the last 6 weeks will be offered HIV testing.

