SFs will be remunerated per specific measurable work activities done in order to track progress and measure costing of the project, while also delivering agreed outputs and maintaining the brand. As such, R40^1^ will be paid per HIV test conducted. This amount remunerates a basic package of HTS services to each client tested that includes consenting a client, conducting an HIV test, distributing condoms, providing client tailor made HIV prevention messages and relevant referrals,^2^ screening for TB and STI and subsequently making necessary referrals, documenting the client. A second, and much bigger remuneration, of R100 will be paid for every HIV positive client linked to HIV care and treatment programmes in the health system. This larger amount is aimed at motivating linkage to care which proved challenging for most counsellors implementing CBCT programmes in the country [33, 34]. SFs will be contracted to test a minimum of 100 clients per month. This minimum requirement was determined by calculating the average time required to conduct HIV testing of an average of 5 people per day while allocating time to conduct other duties including mobilisation, documentation and business management aspects. In order to motivate the SFs to study communities to identify and target HIV hotspots [35, 36], it is a contractual requirement to find at least 5 HIV positive individuals in the 100 people tested. This translates to a minimum 5% HIV positivity target in Tshwane district. The target for linkage to care was at least 4 (80%) of the 5 HIV positive clients being linked to care. Consideration was made of the challenges of linkage to care based on FPD’s experience of running the CBCT programme. The project will review the targets upwards once SFs demonstrated delivery of adequate and quality work in order to align to the UN 90–90-90 target for South Africa to link 90% of the HIV positive people identified [30, 37]. Regular (weekly, bi-monthly, monthly, and quarterly) reports, field visits and observations will be made by FPD to monitor program performance and address any challenges. FPD will audit the SFs’ work and provide regular feedback to SFs to assess their progress. The same linkage to care process as in the FPD HTS will be followed by counsellors.

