### Outcomes

The study has four primary outcomes for programme success: 1) *HIV testing uptake rate,* is defined as all clients who received a basic package of HTS, including HIV testing, divided by the total number of clients offered HIV testing multiplied by 100, 2) *HIV positivity* is defined as the number of clients testing HIV positive divided by the total number of clients tested for HIV multiplied by 100, 3) *Linkage to HIV care and treatment rate* is a proportion of all clients tested positive during the current reporting period and successfully linked to care, divided by the number of all HIV positive clients referred for linkage during the current reporting period multiplied by 100. 4) *Average Counsellors’ remuneration cost* per person tested, per HIV positive test and per person linked to care will be calculated to determine the average cost of employing counsellors in each study group per outcome described above. Secondary outcomes include 5) *App use rate,* is the total number of participants whose data were primarily captured on the app divided by the total number of clients tested multiplied by 100, 6) *First time HIV testers rate* is the proportion of persons identified as testing for HIV for the first time divided by the total number of people tested in a given period multiplied by 100, 8) *Couples HIV testing rate* is defined as the proportion of two people, identifying themselves as partners, testing and receiving results together divided by the total number of clients testing multiplied by 100.

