### Measures

HIV testing and counselling will be conducted following the South African algorithm [38]. An HIV positive status will be assessed by a first test using Alere Determine HIV-1/2 Rapid Test (Alere Medical Co. Ltd., Matsudo-Shi Chiba, Japan) which, if positive, will be confirmed by Abon HIV 1/2/0 Tri-Line Rapid Test (Abon Biopharm, Hangzhou, R. R China). In case of discordant results, final results will be confirmed by Western Blot. Data collected to facilitate linkage to care include a participant’s national ID number, age, gender, place of residence, testing place name, sub district, two telephone/mobile phone numbers, referral clinic name, and client register number. In couples testing, identifying personal data will be collected to assess discordant results. Participants will be asked if they identify themselves as belonging to any key population groups including female sex workers (FSWs), men who have sex with men (MSM), injection drug users (IDUs), and if they are clients of sex workers.

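### Positivity and linkage count people already diagnosed or in care, and repeat testers, while only the SF arm is paid and set quotas on these counts, so the comparison can favour SF without more new diagnoses

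*Protocol article*

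**What the plan says.** - **Eligibility.** Protocol article, Participant inclusion criteria: testing is offered to "any person aged 12 months or older, living in the study community and not having tested for HIV in the last 6 weeks". No other limit on testing history is given.
- **Positivity.** Outcomes: it is "the number of clients testing HIV positive divided by the total number of clients tested for HIV multiplied by 100".
- **Linkage.** Outcomes: it "is a proportion of all clients tested positive during the current reporting period and successfully linked to care". The denominator is every positive client sent for linkage in that period. Under Control arm, links are confirmed in clinic registers and Tier.net. Under Intervention arm, SFs follow the same process.
- **SF incentives.** Intervention arm: SFs receive R40 per test and R100 per linked positive client, with a target of linking 4 of every 5 positives. The section adds that "it is a contractual requirement to find at least 5 HIV positive individuals in the 100 people tested". SFs also choose each day where to test and which demographic groups to target.
- **Control pay.** Control arm and Table 2: a fixed monthly salary that need not depend on testing output.
- **Data collected.** Measures: items include "national ID number, age, gender, place of residence, testing place name, sub district", and whether the client has tested before or is a first-time tester. Follow up adds the date of linkage.
- **Analysis.** Data analysis: arms are compared by gender and age group. No split by earlier diagnosis or care status is described.
- **Context.** Background: Gauteng has 17.6% HIV prevalence and a "lower (75%) than national average (86%) proportion of people who know their HIV status".

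**The concern.** A person diagnosed years ago can be tested, counted as positive, found in a clinic register or Tier.net where they already appear, and counted as linked. Under the written definitions this is a success on both outcomes, although nobody new has been found or brought into care. The same rules apply in both arms, but the reasons to use them do not. To an SF, a positive client already in care is worth R40 + R100 = R140, against R40 for a negative client. That client also helps meet the positivity requirement and needs the least linkage effort. A salaried counsellor gains nothing from such a test.

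Three of the four primary outcomes are exposed: positivity, linkage, and remuneration cost per positive and per link. Strata of age and gender cannot separate new from earlier diagnoses, so the planned comparison would not reveal the problem.

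**Working it through.** **The plan's own figure.** 19 counsellors × 100 clients × 24 months = 45,600 per arm, and × 2 = 91,200, as stated under Sample size and sampling. At 12 months it is 22,800 per arm. Nothing described there makes these counts distinct people.

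**Inputs.** From Background: prevalence 17.6% and awareness 75%, read as a share of people with HIV. Assumed, because the document gives no value:
- f, the fraction of known positives tested, relative to other residents, in one arm only;
- L = 60%, true linkage among clients not in care;
- s, the share of counted positives already in care.

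**Positivity.**
- Undiagnosed: U = 0.176 × 0.25 = 0.044.
- Known positive: K = 0.176 × 0.75 = 0.132.
- Positivity = (U + fK) / (1 − K + fK).
- f = 0: 0.044 / 0.868 = 5.07%, about the SF minimum of 5%.
- f = 5%: 0.0506 / 0.8746 = 5.79%.
- f = 10%: 0.0572 / 0.8812 = 6.49%.
- f = 20%: 0.0704 / 0.8944 = 7.87%.
- f = 100%: 17.6%, the full prevalence.

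**Quota.** The binomial chance of at least 5 positives in 100 tests is 0.58 at 5.07% and 0.79 at 6.49%, so testing known positives makes the requirement easier to meet.

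**Cost.** The SF test fee per positive found is R40 / positivity: R40 / 0.0507 = R789 at f = 0, and R40 / 0.0649 = R616 at f = 10%. The number of new diagnoses among people not known positive is unchanged.

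**Linkage.** If clients in care are referred and count as linked, reported linkage = L(1 − s) + s.
- s = 10%: 0.54 + 0.10 = 64%.
- s = 20%: 0.48 + 0.20 = 68%.
- s = 50%: 0.30 + 0.50 = 80%, the SF target.

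**Would it show as a difference between arms?** Assume independent clients and two-sided 5% significance (the plan states only 95% intervals). With f = 5% in one arm and 0 in the other, a significant difference in positivity appears with probability 0.998 at 45,600 per arm and 0.92 at 22,800. For linkage, with 2,280 positives per arm (5% of 45,600) and s = 10% in one arm only, the probability is 0.80. Clustering by counsellor would lower these probabilities if the analysis allowed for it, but would not remove the shift.

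**The case against.** The strongest reply is that the document shows an opening and an incentive, not that the outcomes are biased. Known positives may be handled in the national testing algorithm, the franchisor's standards or the full protocol, none of which is shown. The franchisor audits SF work and facilitates verification of linkage, and linkage dates are collected, so a link that predates the test could be detected. The linkage denominator is clients referred, so someone in care who is not referred leaves it. Part of any positivity gain is also intended, since the SF requirement is meant to direct testing to hotspots.

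Much of this stands, and it limits the point. These safeguards are real, but the article ties none of them to the outcome definitions or the analysis. The linkage numerator is not expressly limited to referred clients either.

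Several stronger readings are not supported:
- A reader might infer that repeat testing also inflates SF positivity. Repeat tests of negatives, also paid at R40, lower it, so the net sign is uncertain. The six-week rule permits many tests per person, but that is a calendar ceiling, not an expected number.
- A reader might assume known positives are 5% of SF tests and none of control tests, giving 0.05 + 0.95 × 0.0507 = 9.8% against 5.1%. Nothing supports that split. It implies f = 0.05 × 0.868 / (0.95 × 0.132) = 35% in one arm and zero in the other, although both go door to door under one rule.
- A reader might conclude that the app lacks an item on an earlier positive result. The article lists only some of at least 54 variables, so this cannot be confirmed.
- A reader might hold that only new diagnoses should count for linkage. The article treats re-linkage and restarting treatment as programme work (Background; Data collection). Dropping everyone with an earlier positive result would discard people the programme seeks.

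**Conclusion.** The point holds as a weakness in the stated definitions. Eligibility admits people already diagnosed or in care, the outcomes count them as successes, and only one arm is rewarded for doing so. Positivity, linkage, and cost per positive and per link can therefore favour SF without more new diagnoses, and the planned strata would not show it. That this will happen, and by how much, is not shown.

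The illustrative range is 5.8% to 7.9% positivity against 5.1%, and 64% to 80% linkage against 60%. It rests on provincial figures that may not fit the purposively chosen sub-districts or the age range from 12 months. It also rests on assumed values of f, s and L, and on one arm alone being affected. Previously diagnosed people who have left care could instead lower linkage.

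**What to change.** Leave who is offered a test unchanged, and change what counts.

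1. **Positivity:** new diagnoses among people not previously known positive, at each person's first study test. De-duplicate across arms by national ID, with a stated fallback match where the ID is missing.
2. **Linkage:** newly diagnosed people plus previously diagnosed people out of care at the test. Count only links dated on or after the test, and exclude those in care at the test according to Tier.net or the clinic register.
3. **Cost:** use the same counts for cost per positive and per link.
4. **Data:** make sure an earlier positive result and current care status are recorded at the test, adding items if they are not already there.
5. **Reporting:** show known positives, those already in care and re-engaged clients separately by arm.

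The cost is revised outcome wording, possibly one or two app items, and matching on IDs and dates that are largely collected already. Headline positivity and linkage may fall, and records without an ID will need extra matching work.
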